### Primary Endpoints

The primary endpoint is a composite of death from any cause and major adverse cardiac and cerebrovascular events (a composite of a recurrence of Takotsubo syndrome, myocardial infarction, stroke or transient ischemic attack, or death from any cause) evaluated during the in-hospital period and at the 1- and 6-month follow-up.

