### Secondary Endpoints

The secondary endpoints are death from any cause, a composite of major adverse cardiac and cerebrovascular events, serum cardiac biomarker cTnI, NT-pro BNP, modified Rankin Scale (mRS) score, Glasgow Outcome Score (GOS), cardiac function determined by echocardiography, ECG changes (QT interval and possible ST elevation), and blood uric acid level measured prior to RIC treatment, at discharge from the NICU, and at the 1- and 6-month follow-up. The average hospitalization duration will be recorded as a secondary endpoint to evaluate the efficiency of RIC.

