### Sample Size

No previous studies have focused on utilizing RIC to prevent TTS in patients after acute stroke. Most existing evidence utilized troponin I assay for the detection of cardiac injury. Power calculations for this proof-of-concept study will be based on serial troponin measurements, taken as continuous outcome variables with a predicted difference. Previous studies on RIC indicated a cardioprotective effect of RIC in reducing troponin levels by 18–62% (45–48). Based on the results of a pilot study in our center (the troponin level decreased by 40%, *n* = 10), we hypothesized a troponin level reduction of 37% with 80% power at the 5% significance level, and we calculated a sample size of 60 patients (*n* = 30 in each arm of the study).

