### Data Management and Statistical Analysis

An electronic database will be established to collect the data. Unique numeric identifiers will be assigned to each patient, which will be included in the study database; any other information related to the patient's identity will be excluded. Patients' identification will be solely used for follow-up purposes. Data safety will be supervised by an independent monitoring committee. Descriptive and summary statistics will be calculated for each treatment group for baseline characteristics. Continuous data will be expressed as means (standard deviations) or medians (interquartile ranges) for non-normal continuous data and ordinal data. Primary and secondary endpoints will be analyzed by the intent-to-treat principle. In univariate analyses, patient- and clinical-related factors will be compared *via* the chi-square, analysis of variance, Student's *t*-test, or Mann–Whitney *U* test, when appropriate, between two groups. The variables in the initial model included age, gender, diabetes status, hypertension, smoking status, serum cardiac biomarkers, blood uric acid, ejection fraction, LVEDD, mRS, and GOS at baseline. The relative prognostic significance of the variables in predicting the primary endpoint, mRS and GOS will be assessed by multivariate Cox regression models. Variables associated with a *p* < 0.10 on univariable analysis were included in the multivariable analysis. Kaplan–Meier plots and log-rank tests will be utilized to compare the mRS and GOS between two groups. A *p* < 0.05 will indicate statistical significance. SPSS 13.0 software (SPSS Inc., Chicago, IL) will be used for all statistical analyses.

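### The 80% power for troponin is stated for all 60 enrolled patients with no visible allowance for missing values, and the tests named do not use the pre-RIC troponin that could offset such loss

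*Protocol article*

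**What the plan says.** All references are to the protocol article.

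- **Sample Size.** The basis is given as follows: "Power calculations for this proof-of-concept study will be based on serial troponin measurements, taken as continuous outcome variables with a predicted difference". The target is then "we hypothesized a troponin level reduction of 37% with 80% power at the 5% significance level", giving 60 patients, 30 per arm. The section gives no SD, no sidedness, no troponin time point or summary measure, and no loss rate.
- **Randomization and Blinding.** Enrolment is 60 patients at 1:1, the same number as calculated.
- **Intervention and Follow-Up.** Blood is drawn before RIC, every 48 h until NICU discharge, and at 1 and 6 months. Controls are sampled at the same times. Follow-up contact may be by visit, records or telephone.
- **Primary Endpoints.** "The primary endpoint is a composite of death from any cause" and major adverse cardiac and cerebrovascular events, to 6 months.
- **Secondary Endpoints.** Troponin is one of these, "measured prior to RIC treatment, at discharge from the NICU, and at the 1- and 6-month follow-up".
- **Data Management and Statistical Analysis.** The two-group methods named are chi-square, analysis of variance, Student's t and Mann–Whitney, used "when appropriate, between two groups". Baseline cardiac biomarkers appear only as candidate variables for the Cox models of the primary endpoint, mRS and GOS.

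**The concern.** The calculated number and the enrolled number are the same. If 30 per arm is just enough for 80% power, every patient without the analysed troponin value takes power below the stated figure. Some loss is foreseeable from the protocol itself. Death is counted as an outcome, subarachnoid haemorrhage up to grade IV is admitted, and a telephone follow-up yields no blood sample.

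The pre-RIC troponin is collected in both arms, yet no method named for comparing the groups on a continuous variable adjusts for it. That leaves unused the cheapest source of precision in the trial.

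At stake is how a null troponin result is read. Troponin is the only outcome with a power statement, and a reader would judge a null result against 80% when the power of the analysis performed may be lower.

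**Working it through.** **Inputs from the article:** 37% reduction, 80% power, 5% significance, 30 per arm, 1:1. **Assumed:** two-sided test; loss of 5%, 10%, 20% or 30%, equal in both arms; baseline correlation r. The article gives none of these assumed values.

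**Step 1. The plan's own figure.** The figure of 60 cannot be reproduced, because a 37% reduction becomes a sample size only with an SD. It can only be solved backwards. For a two-sample t-test with n per arm, the noncentrality is d × √(n/2) with 2n − 2 degrees of freedom. Setting n = 30 and power = 0.80 gives d = 0.736 (noncentrality 0.736 × √15 = 2.85).

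The SD this implies is:
- raw scale: 0.37 / 0.736 = 0.50 of the control mean;
- log scale: −ln(0.63) / 0.736 = 0.462 / 0.736 = 0.63.

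The normal approximation gives d = 0.723; a one-sided 5% test would give 0.642.

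**Step 2. Unadjusted power under loss, d held at 0.736.**

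| Values missing | n per arm | d × √(n/2) | Power |
|---|---|---|---|
| 0% | 30 | 2.85 | 80.0% |
| 5% | 28.5 | 2.78 | 77.9% |
| 10% | 27 | 2.70 | 75.6% |
| 20% | 24 | 2.55 | 70.4% |
| 30% | 21 | 2.38 | 64.3% |

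**Step 3. Adjustment for pre-RIC troponin.** Analysis of covariance multiplies the residual SD by √(1 − r²), so the effective difference is 0.736 / √(1 − r²), with one fewer degree of freedom.

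- At 20% loss (24 per arm): power is 74.3% for r = 0.3, 82.1% for r = 0.5 and 93.7% for r = 0.7.
- At 10% loss (27 per arm): power is 86.5% for r = 0.5.
- The correlation that brings power back to 80% with 60 enrolled is about 0.32 at 10% loss and 0.46 at 20% loss. The large-sample rule r = √(loss) gives nearly the same: √0.10 = 0.32 and √0.20 = 0.45.

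**Step 4. How far the missing SD matters.** With all 60 patients and an unadjusted t-test, power for a 37% reduction is 94% if the SD is 0.40 of the control mean, 88% at 0.45, 65% at 0.60 and 29% at 1.0. At 0.45, 24 per arm still gives 79.6%. At 0.60, 20% loss lowers 65% to 55%. Uncertainty about the SD therefore moves power more than plausible loss does.

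**The case against.** The strongest objection is that the loss calculation takes the 80% as exact when nobody can check it. Without an SD, the 60 may have been rounded up or may already hold a margin; at an SD of 0.45 of the control mean, a 20% loss would cost essentially nothing against 80%. This stands, and it is why the power figures are only conditional.

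A reader might infer that realistic power is 70–76% because death is part of the primary endpoint. The documents do not support that. They give no loss rate, and the Exclusion Criteria remove patients in an extremely critical condition or thought very unlikely to complete. Nor does a death within 6 months by itself remove a troponin value: sampling runs every 48 h in the NICU, so a patient who dies later still contributes early post-treatment values. Loss would matter most if the 1- or 6-month value were the one analysed, and the article does not say which it is.

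It can also be said that the statistical section does not assign a test to troponin, that a t-test on change would use the baseline, and that the calculation may already be baseline-adjusted, since the pilot's 40% decrease could be a within-patient change. In that last case the gain in Step 3 is already counted. This limits the claimed recovery. It does not alter the fact that no baseline-adjusted troponin comparison is named.

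Finally, the loss of power is 2 to 4 points at 5–10% missing, on a secondary endpoint of a proof-of-concept study. That sets the severity.

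**Conclusion.** The point holds as a minor one. The power statement applies to the full enrolled 60 and shows no allowance for missing troponin. If the 80% is exact at 30 per arm, an unadjusted comparison has about 78%, 76% or 70% power at 5%, 10% or 20% loss. This rests on a two-sided test, a back-solved difference of 0.736, equal loss in the arms, and loss rates that are assumed.

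The article contains no demonstrated arithmetic error: its 80% is unverifiable rather than shown to be wrong. The absent SD is the larger gap in the same paragraph and should be closed in the same edit. The more useful part of the finding is that a baseline value already collected in both arms could offset moderate loss without enlarging the trial, unless the calculation already relied on it.

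**What to change.** **In Sample Size:** state that 80% applies to 60 evaluable patients in an unadjusted two-sided comparison (or whichever form was in fact used). Name the assumed SD and its scale, and the troponin time point or summary. Add the conditional power, for example: about 76% if 10% of values are missing and about 70% if 20% are missing, without baseline adjustment. Label these figures as unadjusted, because they do not describe the analysis below. If the SD actually used differs from the implied one, recompute them. Say whether the calculation already assumed baseline adjustment.

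**In Data Management and Statistical Analysis:** specify that log post-treatment cTnI at the named time point is compared by analysis of covariance with treatment and log pre-RIC cTnI as terms. Give its expected power under a stated correlation, for example about 86% at 10% loss and 82% at 20% loss if r = 0.5.

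Baseline adjustment recovers precision only. It does not remove bias if the values are missing because of death, which is a further reason to name a time point with little loss.

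**Cost:** a few sentences. Keep 60 patients; no new data or visits are needed.

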### Data Management and Statistical Analysis

An electronic database will be established to collect the data. Unique numeric identifiers will be assigned to each patient, which will be included in the study database; any other information related to the patient's identity will be excluded. Patients' identification will be solely used for follow-up purposes. Data safety will be supervised by an independent monitoring committee. Descriptive and summary statistics will be calculated for each treatment group for baseline characteristics. Continuous data will be expressed as means (standard deviations) or medians (interquartile ranges) for non-normal continuous data and ordinal data. Primary and secondary endpoints will be analyzed by the intent-to-treat principle. In univariate analyses, patient- and clinical-related factors will be compared *via* the chi-square, analysis of variance, Student's *t*-test, or Mann–Whitney *U* test, when appropriate, between two groups. The variables in the initial model included age, gender, diabetes status, hypertension, smoking status, serum cardiac biomarkers, blood uric acid, ejection fraction, LVEDD, mRS, and GOS at baseline. The relative prognostic significance of the variables in predicting the primary endpoint, mRS and GOS will be assessed by multivariate Cox regression models. Variables associated with a *p* < 0.10 on univariable analysis were included in the multivariable analysis. Kaplan–Meier plots and log-rank tests will be utilized to compare the mRS and GOS between two groups. A *p* < 0.05 will indicate statistical significance. SPSS 13.0 software (SPSS Inc., Chicago, IL) will be used for all statistical analyses.

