#### Inclusion Criteria

Patients diagnosed with acute stroke (ischemic or haemorrhagic), which can be confirmed on computed tomography (CT) or MRI;Patients diagnosed with subarachnoid hemorrhage with Hess–Hunt grades I–IV;Patients aged 18–75 years;Patients admitted to hospital within 48 h of acute stroke onset;Patients diagnosed with Takotsubo syndrome with an InterTAK diagnostic score ≥50 (6). The ventricular wall motion will be evaluated with echocardiography. If acute coronary syndrome (ACS) is suspected based on ECG, echocardiography, or biomarker findings, coronary computed tomography angiography (CTA) will be conducted to rule out ACS. Coronary angiography and cardiac magnetic resonance imaging will be utilized to differentiate ACS only when necessary.Patients with a signed written informed consent form.

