### Randomization and Blinding

A total of 60 eligible patients with acute stroke, in accordance with the inclusion and exclusion criteria, will be included in this study. Random numbers will be generated on a computer by an unblinded physician who will not be involved in the data analysis and then placed in sealed envelopes. The patients will be randomly allocated into either the RIC or the control group according to a ratio of 1:1. The physician responsible for performing RIC will not be blinded and will play no further role in the clinical trial; the staff responsible for the data collection and analysis will be blinded. Hence, this is an outcome-assessor-blinded study.

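### The only method named for the primary composite is a prognostic Cox model with 11 to 12 candidates screened at p < 0.10 and no randomised arm

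*Protocol article*

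**What the plan says.** All of this is in the Protocol article, Data Management and Statistical Analysis, unless another section is named.

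- **Candidate list.** "The variables in the initial model included age, gender, diabetes status, hypertension, smoking status, serum cardiac biomarkers, blood uric acid"; the list then continues with ejection fraction, LVEDD, mRS and GOS, all at baseline. Randomised arm is not on it.
- **Purpose of the Cox model.** "The relative prognostic significance of the variables in predicting the primary endpoint", together with mRS and GOS, is what the multivariable Cox models are to assess.
- **Entry rule.** Variables with p below 0.10 "on univariable analysis were included in the multivariable analysis".
- **Comparisons between arms.** Kaplan–Meier plots and log-rank tests between the two groups are named for mRS and GOS. Chi-square, t, analysis-of-variance and Mann–Whitney tests between the two groups are described for patient and clinical factors. Primary and secondary endpoints are to follow intention to treat, but that sentence names no test or estimator.
- **Endpoint and size.** Primary Endpoints defines a composite of death and major cardiac and cerebrovascular events, in hospital and at 1 and 6 months. Randomization and Blinding has patients "randomly allocated into either the RIC or the control group according to a ratio of 1:1", and in Sample Size "we calculated a sample size of 60 patients".

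**The concern.** The Objectives section asks whether RIC improves heart function and clinical outcomes, so the primary analysis has to yield a contrast between arms on the composite. The one model attached to that composite answers a different question, namely which baseline factors predict it. An analyst who followed the text literally could complete the stated Cox analysis and have no RIC effect to report.

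The model is also built in a way that 60 patients cannot support. Choosing among 11 or 12 candidates by univariable p-value lets chance decide which covariates appear, and the p-values printed for the survivors ignore that they were chosen for being small. Any statement about independent predictors of the composite would be fragile.

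This is not a complaint about detail left to a statistical analysis plan. The article itself fixes the model, its candidates and its selection rule, and an analysis plan that followed it would inherit all three.

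**Working it through.** **Inputs from the article.** N = 60, 30 per arm. Candidates k = 11 as listed, or 12 if serum cardiac biomarkers means cTnI and NT-pro BNP, the two named in Secondary Endpoints. Screening level 0.10; significance level 0.05. The article gives no event rate and no hazard ratio for the composite, so event rates below are assumptions.

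**The plan's own figure.** N = 60 rests on troponin: "we hypothesized a troponin level reduction of 37% with 80% power at the 5% significance level". No standard deviation is given, so it cannot be reproduced. Solved backwards (two-sided), it needs a standardised difference of (1.960 + 0.842) × √(2/30) = 0.723. That means an SD of 0.37/0.723 = 0.51 of the control mean or, on the log scale, |ln 0.63|/0.723 = 0.64. What matters here is only that the power calculation says nothing about how many composite events to expect.

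**Step 1: which method gives an arm contrast on the composite?**

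| Method named | Applied to | Compares arms? |
|---|---|---|
| Multivariable Cox | composite, mRS, GOS | no; arm not listed |
| Kaplan–Meier, log-rank | mRS, GOS | yes |
| Chi-square, t, ANOVA, Mann–Whitney | patient and clinical factors | yes |
| Intention to treat | primary and secondary endpoints | a principle; no method attached |

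No row names both the composite and a comparison of arms.

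**Step 2: events per candidate** = 60 × event rate / k.

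| Event rate | Events | k = 12 | k = 11 |
|---|---|---|---|
| 10% (assumed) | 6 | 0.5 | 0.55 |
| 20% (assumed) | 12 | 1.0 | 1.09 |
| 30% (assumed) | 18 | 1.5 | 1.64 |
| 40% (assumed) | 24 | 2.0 | 2.18 |
| 50% (assumed) | 30 | 2.5 | 2.73 |
| 100% (ceiling) | 60 | 5.0 | 5.45 |

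The last row needs no assumption about the event rate: the ratio cannot exceed 5.0 to 5.5.

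**Step 3: what the screen lets through if every candidate is independent noise.**

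- Expected number passing: 12 × 0.10 = 1.2 (11 × 0.10 = 1.1).
- At least one passes: 1 − 0.9^12 = 0.718 (1 − 0.9^11 = 0.686).
- At least two pass: 34% for 12 candidates, 30% for 11.

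**Step 4: what then appears in the final model.** A null simulation used 60 patients, 12 independent noise covariates, the univariable screen at 0.10 followed by Cox, and 300 runs at each of 20%, 30% and 50% events. On average 1.18 to 1.27 covariates passed. In 42–43% of simulated trials the final model held at least one noise covariate at p < 0.05, the article's own threshold. The Monte Carlo standard error is √(0.43 × 0.57/300), about 3 percentage points.

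**The case against.** **The Cox model is prognostic by design.** A model meant to rank prognostic factors need not contain arm, and leaving arm out is no error within that model. The article also promises an intention-to-treat analysis of the primary endpoint and lists two-group tests in the next sentence. In a condensed article, an unadjusted comparison of the composite by arm is a fair guess at what is meant, and an analysis plan may say so. This stands, and it limits the point: the text does not show that no arm comparison will be made. It shows that the one method attached by name to the composite is not such a comparison.

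**The noise figures are a reference case.** Nothing in the article makes age, ejection fraction or baseline mRS pure noise, and pairs such as mRS and GOS are plausibly correlated, which would lower the 72%. If all were noise, only about 1.2 variables would reach the final model, so events per candidate is not the fitted model's ratio. This also stands. The instability comes from selecting across all candidates at least as much as from the size of the final model.

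**Stronger readings that the article does not support.**

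- A reader might infer that the screen would usually drop treatment. Arm is not a candidate, so it cannot be screened out. A drop-out rate would also need a hazard ratio for the composite, and the 37% in Sample Size is a troponin reduction, not a hazard.
- A reader might infer that the standard error of the RIC effect will be too small. Baseline covariates are independent of arm by randomisation, so the harm shown falls on the covariates' own p-values. Nothing here shows it for RIC.
- A reader might infer that a decisive covariate, stroke type, is missing. Inclusion Criteria admits both ischaemic and haemorrhagic stroke and the list omits type, but the article gives no outcomes by type. That it drives the result would be an assumption.

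**Conclusion.** The point holds in two parts.

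1. As written, the only analysis tied by name to the primary composite does not estimate the RIC effect. This rests on the text alone. It is a defect in what is stated, and does not prove that a comparison by arm is absent from the investigators' intentions.
2. The prognostic model is unreliable. The ceiling of 5.0 to 5.5 events per candidate holds at any event rate; the 1 to 2 per candidate rests on an assumed 20–40% event rate. The 72% (69% for 11) and the simulated 42–43% rest on independent noise candidates and illustrate how permissive the screen is. They do not forecast this trial's result.

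The text should be corrected. The finding does not touch the validity of randomisation or show bias in any treatment estimate.

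**What to change.** - State the primary analysis as an intention-to-treat comparison of the composite by randomised arm: log-rank test, plus a Cox model in which arm is always included and is never subject to a p-value rule.
- Adjust for at most one or two baseline covariates already collected, for example age, fixed before outcome data are seen. Remove the p < 0.10 screen.
- Keep the multi-variable prognostic model, if wanted, as explicitly exploratory and without univariable screening; a penalised fit is one option.

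**Cost.** Wording only: no extra patients, visits or data. The downside is that fewer covariates are examined in the confirmatory model. Restraint is needed even so: at the assumed 12 to 24 events, arm plus two covariates gives 12/3 = 4 to 24/3 = 8 events per parameter, arm plus one gives 6 to 12, and arm alone 12 to 24. This is why the unadjusted result should be reported alongside.

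### Kaplan-Meier, log-rank and Cox methods are assigned to the mRS and GOS, which are ordinal scores taken at fixed visits with no event or event time

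*Protocol article*

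**What the plan says.** In the protocol article, Data Management and Statistical Analysis, the arm comparison of the two functional scales is fixed in one sentence: Kaplan-Meier "plots and log-rank tests will be utilized to compare the mRS and GOS between two groups". A sentence shortly before it gives the modelling approach, in which the prognostic value of baseline variables for "predicting the primary endpoint, mRS and GOS will be assessed by multivariate Cox regression models".

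Secondary Endpoints lists the two scales as scores, alongside other measurements: "modified Rankin Scale (mRS) score, Glasgow Outcome Score (GOS), cardiac function determined by echocardiography". The list ends with the times at which they are "measured prior to RIC treatment, at discharge from the NICU, and at the 1- and 6-month follow-up". Table 1, under Intervention and Follow-Up, ticks mRS or GOS at admission, NICU discharge, and 1 and 6 months after discharge.

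The same statistical section treats ordinal data as a type of its own, to be summarised as "medians (interquartile ranges) for non-normal continuous data and ordinal data". It also names the Mann-Whitney U test, but for a different purpose: "In univariate analyses, patient- and clinical-related factors will be compared" by that test, among others.

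**The concern.** A log-rank test or Cox model needs three things for each patient: a defined event, a time at which it happened, and an indicator of whether follow-up ended first. An ordinal score read at scheduled visits supplies none of them. To carry out the stated analysis, someone must choose a cut-point, decide that the visit date stands for the event time, set a time origin, and decide what happens to patients who die. None of these choices is stated, and they could be made after data have been seen.

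The handling of death matters most. Death is the worst category of both scales (mRS 6, GOS 1). If the event were reaching a good score and deaths were censored, the worst outcome would drop out of the functional comparison. These are the trial's only functional neurological outcomes, in a population of stroke patients.

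**Working it through.** **1. What the method needs against what the article gives for mRS and GOS**

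| Needed for log-rank or Cox | Given in the article |
|---|---|
| Event or threshold | None; both are listed as scores |
| Event time | None; only scheduled assessments |
| Time origin | None; the 1- and 6-month visits are counted from discharge |
| Censoring rule | None |
| Place of death | Not stated |

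This mismatch is enough for the point. The calculation below only shows how much the answer can move.

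**2. The plan's own figure.** No power, event count or sample size is given for mRS or GOS. The only sample size, 60, rests on "a troponin level reduction of 37% with 80% power at the 5% significance level". No SD is stated, so it can only be solved backwards (two-sided, 30 per arm). The detectable standardised difference is (1.960 + 0.842) × √(2/30) = 2.802 × 0.258 = 0.723, which implies an SD of 0.37/0.723 ≈ 0.51 of the control mean. This neither confirms nor refutes 60, and nothing below depends on it.

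**3. Simulation inputs**
- From the article: 30 per arm, 5% significance level (taken as two-sided).
- Assumed: mRS 0 to 5 among survivors has probabilities 0.10, 0.15, 0.20, 0.20, 0.20, 0.15 in both arms. Good function is mRS 0–2, with probability 0.10 + 0.15 + 0.20 = 0.45. It is first seen at 0.5, 1 or 6 months (0.2, 0.3, 0.5). Deaths fall at 0.25, 0.75 or 3 months (0.5, 0.3, 0.2).
- 3,000 simulated trials per row. The Monte Carlo standard error is √(0.05 × 0.95/3000) = 0.4 percentage points near 5%, and √(0.5 × 0.5/3000) = 0.9 points near 50%.

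**4. Tests compared.** The log-rank statistic is (O − E)²/V on 1 degree of freedom, under three readings of the sentence:
- A: time to first visit with mRS 0–2, deaths censored at death.
- B: as A, but deaths kept at risk to 6 months without the event.
- C: the score itself used as the time axis, death at 6, everyone an event.

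The comparators are Mann-Whitney on mRS with death scored 6, and an uncorrected chi-square test on deaths.

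**5. Percentage of trials with p < 0.05**

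| Mortality, control vs RIC | A | B | C | Mann-Whitney | Deaths, chi-square |
|---|---|---|---|---|---|
| 20% vs 20% | 4.4 | 4.4 | 4.6 | 4.3 | 4.4 |
| 40% vs 40% | 5.3 | 5.5 | 4.9 | 5.0 | 4.9 |
| 30% vs 10% | 4.8 | 10.7 | 39.8 | 26.1 | 49.2 |
| 40% vs 10% | 5.4 | 19.1 | 71.2 | 53.0 | 80.1 |
| 50% vs 10% | 5.6 | 31.8 | 90.2 | 79.3 | 94.5 |

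A second simulation of 40% versus 10%, with other assumed timings (2,000 trials, deaths at day 5, visits at days 20, 50 and 200), gave 4.45% for reading A and 58.7% for Mann-Whitney.

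**6. Why A and B differ.** At 40% versus 10% mortality, good function is reached by 0.60 × 0.45 = 27.0% of control patients and 0.90 × 0.45 = 40.5% of RIC patients. Reading B keeps that difference. Reading A removes the dead from the risk set and compares recovery among those still alive, which was set equal in the two arms.

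**The case against.** The strongest reply is that this is a condensed article, that thresholds and censoring rules normally sit in a full protocol or SAP, and that time to first visit at a favourable score is a definable analysis. That holds for the missing details. It does not hold for the method: the article names a test for an ordinal score and names the wrong kind. An SAP that followed the sentence would inherit the problem, and one that corrected it would depart from the published text.

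Other objections stand and limit the point.

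- A reader might infer that the trial would overlook a mortality difference. The documents do not support this. No rule says that deaths are censored; reading A is one possibility among several, and reading C rejects more often than Mann-Whitney. Death is also assessed separately: "The secondary endpoints are death from any cause, a composite of major adverse cardiac and cerebrovascular events". It is part of the primary composite as well, and an independent committee monitors the study.
- The simulation fixes equal recovery in survivors, so the null-level rejection under reading A is correct behaviour for the question that reading asks. It shows that the question leaves out death, not that the test misbehaves.
- A reader might infer that the test gives false positives. With equal mortality, every method rejected in about 4% to 6% of trials.
- A reader might infer that the primary endpoint has no time-to-event method. The Cox sentence does name it as an outcome, and a missing log-rank comparison is something an article may leave to the SAP.
- The Cox sentence concerns prognostic factors. The arm comparison of mRS and GOS rests on the Kaplan-Meier and log-rank sentence alone.

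**Conclusion.** Wrong as written; should be fixed. The article assigns survival methods to two ordinal scores for which it gives no event or event time, although it recognises ordinal data and names a suitable rank test elsewhere in the same section. Under assumed mortality of 40% versus 10%, one sentence allows rejection rates from about 5% to 71%, depending on definitions that the analyst would have to supply. If deaths were censored, the functional comparison would be blind to a mortality difference.

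The harm is confined to the mRS and GOS comparisons. It does not reach the primary endpoint, the separate assessment of death or the sample size, which is why this falls short of a must-fix. The method mismatch follows from the text alone. The percentages rest on assumed mortality, mRS distribution and timing, and are illustrations rather than predictions for this trial.

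**What to change.** Delete mRS and GOS from the Kaplan-Meier/log-rank sentence and from the outcomes of the Cox models. In their place, state:

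- mRS and GOS will be compared between randomised arms as ordinal outcomes at one named visit (6 months after discharge is one candidate), using the Mann-Whitney U test already listed or a proportional-odds model with arm, reporting a common odds ratio and 95% confidence interval.
- Patients who have died by that visit will be placed in the worst category (mRS 6, GOS 1).
- Kaplan-Meier curves and the log-rank test will compare the arms for time to first primary composite event and for time to death.

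Which visit and which of the two ordinal methods to use is for the trial team to choose, but the choice should be fixed before unblinding. The cost is a few sentences of analysis wording. No new data are needed, since the scores and deaths are already collected at these visits.
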